### Sample size

Based on the reviewed literature, we predict a small-medium effect size (*f* = 0.14) on the primary variable. The sample size for this study is 150 participants, with 50 participants in each treatment group (Lacprodan® PL-20, MPC or rice starch). Allowing for a 20% drop-out rate over the course of the 180-day testing period, this will give 80% power to detect significant treatment × time interactions from baseline to 180 days for the primary outcome (calculated using G*Power 3.1, with α = 0.05 and *r* = 0.5 for the correlation between repeated measures).

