### Analysis

The primary analysis will investigate the effect of treatment on all cognitive outcomes from baseline to 180 days, using the groups as randomized (intention to treat). Statistical analyses will be conducted using linear mixed modelling, whereby subject-specific random intercepts and slopes will be fitted to subject data and fixed effects will be fitted to treatment group, time and the treatment × time interaction. On the basis of *APOE* and *MTHFR* genotyping, subgroup analysis will also be conducted in order to investigate the effect of allelic differences on treatment response. Secondary outcome variables will be analysed using similar statistical techniques. Results will be considered statistically significant at an alpha level of *P* <0.05 corrected for multiple comparisons.

Although stratification according to age, intelligence and baseline WMS-R scores may help to explain some of the residual between-group variance unrelated to the treatment effect, further exploration of possible covariates will also be investigated. Baseline correlations between the primary cognitive outcome measures and other baseline variables, including BMI, educational background, diet, CV function, GI microbiota and biochemical parameters, will also be investigated in order to investigate other important covariates. In the event that significant correlations at the *P* <0.05 level are found at baseline then these additional variables will also be controlled for in the primary analysis of cognitive outcomes.

Analysis of functional neuroimaging data (both MEG and fMRI) during episodic memory and N-Back working memory tasks will be conducted using a region of interest (ROI) approach. Using this method, between-group (Lacprodan® PL-20 versus MPC and inert placebo) functional differences in predefined brain regions will be statistically analysed. The ROIs for the episodic memory task will include the medial temporal lobes, the lateral prefrontal cortices, the associative temporal and paretial regions, the cingulate gyrus and the cerebellum. The ROIs that will be analysed in the N-Back working memory task will include the dorsolateral, ventrolateral and medial prefrontal cortex, anterior cingulate, parietal cortex and sensorimotor cortex [136].

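### The stated 80% power is for an omnibus interaction at uncorrected 0.05; it does not cover the two pairwise hypotheses under the corrected significance rule, and small-medium understates the assumed effect

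*Protocol article*

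**What the plan says.** **Protocol article, Sample size.** The effect assumption reads "we predict a small-medium effect size (*f* = 0.14) on the primary variable". Enrolment reads "The sample size for this study is 150 participants, with 50 participants in each treatment group". Power is given as "Allowing for a 20% drop-out rate over the course of the 180-day testing period, this will give 80% power" for treatment × time interactions between baseline and day 180, computed in G*Power 3.1 "with α = 0.05 and *r* = 0.5 for the correlation between repeated measures". The number of measurement occasions entered is not given.

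**Abstract (Methods) and Table 2.** The primary outcome is assessed after enrolment at baseline, day 90 and day 180, so either two or three occasions could have been entered.

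**Aims and study hypotheses.** Two comparators are used because they answer separate questions. PL-20 against rice starch asks whether the product works as a whole. PL-20 against the phospholipid-free milk protein concentrate (MPC) asks whether the phospholipids are responsible. The second comparison is expected to show a smaller benefit.

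**Analysis.** Significance is declared at P < 0.05 "corrected for multiple comparisons". Neither the method nor the number of comparisons is stated. The same section describes the primary analysis as covering all cognitive outcomes.

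**The concern.** Power is a property of a particular test at a particular significance level. The Sample size section describes one test (a three-arm interaction at uncorrected 0.05), while the hypotheses and the Analysis section describe another (two pairwise contrasts, judged after correction). A reader would take the 80% to apply to the hypotheses.

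The effect-size label adds to this. In the G*Power interaction module f is not a standardized difference between two arms. The same f can correspond to a considerably larger difference in change than the words small-medium suggest.

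At stake is how a null result is read, above all for PL-20 versus MPC. That is the only contrast that isolates the phospholipids, and the article itself expects it to be the smaller one. A non-significant result there could be taken as evidence against a small-medium phospholipid effect that the trial had little chance of detecting.

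**Working it through.** **Inputs (Sample size section):** k = 3 arms, 150 randomized, 20% drop-out, so N = 150 × 0.8 = 120 (40 per arm); f = 0.14; r = 0.5; α = 0.05. The number of occasions m is not stated, so m = 2 and m = 3 are both tried.

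**Step 1. Reproduce the 80%.** G*Power within-between interaction, default effect-size option, sphericity assumed: λ = N·m·f²/(1 − r), df1 = (k − 1)(m − 1), df2 = (N − k)(m − 1).

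- m = 2: λ = 120 × 2 × 0.0196/0.5 = 9.408, df 2 and 117, power 77.9%.
- m = 2 with f = 0.1435, which prints as 0.14: power 80.0%.
- m = 3: λ = 120 × 3 × 0.0196/0.5 = 14.112, df 4 and 234, power 86.2%.

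The alternative G*Power option (effect size as in Cohen) gives about 25% with m = 2, so the default option was evidently used. The stated figure is recovered within the rounding of f.

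**Step 2. Translate f into a difference in change.** With two occasions, f equals half the SD, across arms, of the mean change (in outcome SD units). That SD is therefore 2 × 0.14 = 0.28.

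- PL-20 differs by D from two equal controls: the SD across arms is D√2/3, so D = 0.28 × 3/√2 = 0.594.
- MPC midway between PL-20 and rice starch: the SD across arms is D/√6, so D = 0.28 × √6 = 0.686. PL-20 versus MPC is then 0.686/2 = 0.343.

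The equal-controls pattern is the limiting case, because the article expects a smaller benefit against MPC. The midway pattern is an assumption; the article gives no figure.

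**Step 3. Pairwise power.** Two-sided t test on change scores, 40 per arm, 78 df. The variance of change is 2(1 − r) = 1.0 SD², so the noncentrality is D/√(2/40) = D/0.2236. The level 0.025 is an assumed equal split over two contrasts.

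| Contrast | Difference (SD) | Noncentrality | Power at 0.05 | Power at 0.025 |
|---|---|---|---|---|
| PL-20 vs rice starch, controls equal | 0.594 | 2.66 | 74.7% | 64.5% |
| PL-20 vs rice starch, MPC midway | 0.686 | 3.07 | 85.8% | 78.1% |
| PL-20 vs MPC, MPC midway | 0.343 | 1.53 | 32.8% | 23.2% |

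**Step 4. Detectable difference.** With the same test and 40 per arm, 80% power needs about 0.63 SD at 0.05 and about 0.70 SD at 0.025.

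**The case against.** **The 80% is not an arithmetic error.** This stands. A reader might infer from 77.9% that the figure is wrong, or that 80% holds only up to 16% drop-out, because m = 2 needs 126 completers out of 150. The document supports neither. Rounding of f closes the gap, and with three occasions 104 completers suffice. The mixed model under intention to treat also uses partial data, so counting only 120 completers is conservative.

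**The correction is unspecified and may be left to an analysis plan that is not shown.** This stands as to size. A reader might infer that power falls to 68%. That figure (68.5%) needs two occasions and applies a split meant for pairwise contrasts to the omnibus test; with three occasions it is 79.0%. A fixed testing order could leave 0.05 for the first contrast, giving 74.7% or 85.8% in the table above. Correction over all cognitive outcomes would lower power further, by an amount the article does not allow one to compute. None of this removes the mismatch between an uncorrected alpha in one section and a corrected one in another.

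**The label fits f as a number.** This is fair: 0.14 can conventionally be called small-medium for f, and the article makes no claim about a standardized difference. A reader might go further and take f = 0.14 as a two-arm difference of 0.28 SD, with 24% pairwise power at 0.05. The article does not say that, and the module does not define f that way. The point is only that the label conceals the implied difference.

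**Three occasions would change Steps 2 and 3.** This is true. If change is linear over the three visits (an assumption), the SD of change across arms is f√6 = 0.343. The implied differences are then 0.343 × 3/√2 = 0.73 SD and 0.343 × √6 = 0.84 SD. The first contrast would then exceed the 0.70 SD needed at 0.025. But the assumed effect is larger still, and PL-20 versus MPC in the midway case (0.42 SD) remains below the 0.63 SD needed even at 0.05.

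**Conclusion.** The concern holds as a mismatch between the power statement and the decision rule. The 80% is approximately right for what was computed: an omnibus three-arm treatment × time interaction at uncorrected 0.05. It is not the power of either pairwise hypothesis at the level the Analysis section requires.

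The size is conditional. With two occasions, change scores, r = 0.5, 40 completers per arm and an assumed 0.025 per contrast, PL-20 versus rice starch has about 65% to 78% power. With MPC midway, PL-20 versus MPC has about 23%, or 33% without correction. The contrast that isolates the phospholipids is therefore the one least covered by the stated figure.

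Under the default G*Power option with two occasions, f = 0.14 assumes a 0.59 to 0.69 SD difference in change, so small-medium misdescribes the assumed effect.

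**What to change.** Restate the Sample size paragraph so that it:

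1. gives the number of measurement occasions entered and the G*Power effect-size option used;
2. says that 80% refers to the omnibus treatment × time interaction at uncorrected α = 0.05;
3. names the alpha the analysis will use for each of the two contrasts, and gives power or detectable difference at that alpha. With 40 per arm, change scores and r = 0.5, 80% power corresponds to about 0.63 SD at 0.05 or 0.70 SD at 0.025;
4. replaces the small-medium label with the implied difference in change, in SD of the RVLT composite, for the assumed pattern across the three arms.

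Do not add a statement that 80% holds only to 16% drop-out, and do not quote 68% as an unconditional figure.

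The cost is one rewritten paragraph with less favourable figures. Enrolment and trial conduct do not change.

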### Treatments

Lacprodan® PL-20, a powdered MPC rich in phospholipids, is manufactured by Arla Foods Ingredients Group P/S, Viby J, Denmark. The content of individual phospholipids in Lacprodan® PL-20 is displayed in Table 1.

**Table 1 T1:** Phospholipid composition of Lacprodan® PL-20 by percentage and daily dose

	**Percentage (%)**	**Minimum dose per day**
Sphingomyelin	4.3	688 mg
Phosphatidyl choline (PC)	4.3	688 mg
Phosphatidyl serine (PS)	1.9	304 mg
Phosphatidyl ethanolamine (PE)	3.5	560 mg
Phosphatidyl inositol (PI)	1.3	208 mg
Ganglioside and others	0.7	112 mg

Lacprodan® PL-20 will be administered orally at a maximum dose of 16 g/day, providing minimum daily dosages of 2.7 g PL and 300 mg PS. The powder is dissolved in 150 to 200 mL water and drunk once per day with breakfast. Two placebo treatments will also be administered: (i) an inert placebo consisting of rice starch (20 g/day), and (ii) an MPC without phospholipids (Arla Foods); (12 g/day). Both placebo treatments are also administered orally as powders dissolved in ≤250 mL water and matched to Lacprodan® PL-20 for colour and taste in order to ensure treatment blinding.

### Randomization and safety

Randomization of participants to treatment groups will be determined by random allocation. For the neuroimaging sub-study 60 randomization numbers will be set aside, which correspond to 10 female participants receiving Lacprodan® PL-20, 10 receiving MPC and 10 receiving rice starch placebo, and 10 male participants receiving Lacprodan® PL-20, 10 receiving MPC and 10 receiving rice starch placebo. Blinding for both the main study as well as the neuroimaging sub-study will be conducted by an independent staff member at the Centre for Human Psychopharmacology, who is outside of the project, to code the treatments, and maintain the key to this code until data collection is completed. All potential adverse events will be monitored throughout the trial, with oversight from the Swinburne University of Technology Human Research Ethics committee.

### Primary outcomes

The primary study outcome is the effect of Lacprodan® PL-20 supplementation on memory as measured using a compound score from the RVLT [69,70], similar to that used previously [71]. The memory score will be derived using the formula:

$$\begin{array}{l} \left(Z_{15‒\mathrm{Word}\;\mathrm{Learning}\;\mathrm{test}‘\mathrm{total}\;\mathrm{immediate}\;\mathrm{recall}}’\right)\\ \;+Z_{15‒\mathrm{Word}\;\mathrm{Learning}\;\mathrm{Test}‘\mathrm{maximum}\;\mathrm{immediate}\;\mathrm{recall}’}\\ \left(\;+Z_{15‒\mathrm{Word}\;\mathrm{Learning}\;\mathrm{Test}‘\mathrm{delayed}\;\mathrm{recall}’}\right)/3. \end{array}$$

The RVLT is a test of verbal learning and memory that has a long history of use both in the assessment of clinical memory disturbances as well as cognitive decline associated with normal ageing [70]. Verbal learning, as measured by the RVLT and similar tests, has previously been found to be sensitive to the effects of phospholipid interventions in AAMI populations [39,41]. Similarly, verbal memory has also been found to be sensitive to other nutraceutical interventions such as *Bacopa monnieri*[72] and folic acid [71] in elderly populations. For these reasons, the inclusion of the RVLT will enable direct comparison of the efficacy of the milk-derived phospholipids present in Lacprodan® PL-20 to previous cognitive intervention studies in the elderly.

### Secondary outcomes

A range of secondary outcomes will be used, encompassing cognitive performance, mood, CV, GI microbiota, biochemical, genetic and brain imaging modalities. Secondary outcomes will include other elements of cognitive performance as measured by a battery of well-validated and highly sensitive cognitive tests. Traditional paper-and-pencil neuropsychological tests as well as computerized tasks have been included. These tests will be implemented at baseline, 90 days and 180 days (pre-dose) in order to capture chronic effects. This battery will consist of the MMSE [65], the Prospective and Retrospective Memory Questionnaire (PRMQ) [73], RVLT [69,70], Spatial Working memory and Contextual Memory tasks from the Swinburne University Computerized Cognitive Ageing Battery (SUCCAB [74]), rapid visual information processing (RVIP), serial 3 s and 7 s subtraction and the Hick’s reaction time paradigm. In order to capture potential acute cognitive effects associated with Lacprodan® PL-20 supplementation, the SUCCAB tests, RVIP, serial 3 s and 7 s subtraction and Hick’s reaction time will also be administered 90 minutes post dose.

The MMSE [65] is a global measure of cognitive function that has been used extensively both as a diagnostic tool for dementia screening as well as a cognitive outcome measure for gauging the efficacy of chronic nutraceutical interventions in elderly participants, for example [71,75,76]. The MMSE was included in the current study due to its widespread use in previous research; however problems with ceiling effects and insensitivity to change amongst high-functioning individuals have been previously well-documented [77].

The PRMQ [73] is a self-report instrument which provides a measure of retrospective as well as prospective memory slips in everyday life. The PRMQ was included in the current study in order to provide an ecologically valid measure of typical memory complaints that may be of concern to elderly individuals. Although most memory complaint questionnaires focus exclusively on failures to remember previous information (retrospective memory), the PRMQ is unique in that it additionally provides a measure of prospective memory failures, which are failures relating to tasks that need to be completed at a certain time (for example, remembering to turn up to an appointment on time) [73,78].

In addition to the use of traditional psychometric tests, the importance of including computerized tests that may accurately gauge the speed of well-differentiated cognitive functions has emerged in recent years [79]. In the current study the spatial working memory and contextual memory tasks from the SUCCAB have been included due to high degrees of sensitivity to the effects of ageing, as measured using response times [74]. Similarly, significant reductions in response times on both of these tasks have previously been reported in older participants following chronic nutraceutical interventions [80,81]. For the assessment of processing speed, the highly sensitive Hick reaction time paradigm [82] will be used. For the assessment of cognitive function during increased demand, serial 3 s and serial 7 s subtraction will be assessed together with the RVIP computerized measure of sustained attention. Previous research from our laboratory has found the serial subtraction and RVIP tasks to be particularly sensitive to the acute effects of nutraceutical interventions [83-86].

#### Mood

There is evidence to suggest that phospholipid supplementation may have a positive effect on chronic stress as well as mood. Mood improvements have been previously reported in a double-blind trial of PS in depressed patients [87]. A number of studies have also demonstrated that phospholipids may have anti-stress effects, as demonstrated by lowered levels of adrenocorticotropic hormone (ACTH), reduction in perceived stress ratings in response to acute stress [88] and reduced cortisol release in response to acute stress [89,90]. In relation to milk-based phospholipids, it was recently demonstrated that chronic supplementation may lead to increased morning cortisol availability in chronically stressed men [91] as well as a blunting of self-report stress ratings in response to an acute stressor [43].

Chronic changes in mood over the course of the trial will be assessed using the Depression, Anxiety and Stress Scale (DASS) [92], the Profile of Mood States (POMS) [93] and Bond-Lader visual analogue mood scales [94]. These measures will be administered at baseline, 90 and 180 days pre-dose. The Bond-Lader scales will additionally be administered post dose at each study visit in order to capture potential acute mood effects associated with Lacprodan® PL-20 treatment. The Bond-Lader scales have previously been used by our group in a wide range of acute and chronic intervention studies, and have been found to display excellent sensitivity to subtle affective changes.

#### Cardiovascular assessment

There is evidence to suggest that increases in arterial stiffness with ageing, which are reflected in measures of blood flow velocity, may be a contributing factor in cognitive decline [95,96]. Previous research suggests that milk proteins may increase insulin secretion, as well as help to reduce blood pressure and plasma cholesterol levels [3,97]. Further, high levels of B12 present in milk may also help to lower HCy levels, which are a contributing factor to CV disease [98]. In light of the fact that Lacprodan® PL-20 is an MPC, it could be argued that chronic supplementation may have a positive influence on CV function. By this reasoning, the inclusion of CV parameters in the current study will enable exploration of whether improvements to CV function are a mechanism by which with Lacprodan® PL-20 may achieve cognitive benefits.

CV function will be assessed using brachial blood pressure, aortic blood pressure, carotid-femoral pulse wave velocity (PWV) as well as blood flow velocity in the medial carotid artery and the common carotid artery (CCA). Brachial blood pressure will be calculated with the participant seated and following a five-minute rest period using a clinically validated automated sphygmomanometer. Aortic blood pressure, pulse pressure and PWV (all aspects of arterial stiffness and CV pressures) will be measured non-invasively using the SphygmoCor device. Applanation tonometry of the radial artery will be used to estimate aortic pressures and wave reflections, and applanation of the carotid and femoral arteries will be used to measure PWV. A non-invasive transcranial Doppler system will be used to record middle cerebral artery (MCA) blood velocity by placing a sensor close to the participant’s ear and common carotid artery (CCA) blood velocity will be recorded by placing a hand-held sensor at the base of the participant’s neck. All CV measures will be assessed pre- and post dose at the baseline, 90-day and 180-day study visits in order to capture both acute and chronic effects associated with Lacprodan® PL-20 supplementation.

#### Gastrointestinal microbiota

In recent years research in the field of GI microbiota has caught major interest. Research is suggesting that modifications in the composition of the GI microbiota influence normal physiological functions and contribute to diseases ranging from inflammation to diabetes. Collectively studies now indicate that the gut microbiota also communicates with the CNS possibly through immune, neural and endocrine pathways, and by these means influences gut-brain communication, brain function and even behaviour [99-101]. Studies on germ-free animals and animals exposed to pathogenic bacterial infections, probiotic bacteria or antibiotics, suggest a role of GI microbiota in the regulation of cognition, anxiety and mood [101-103]. Moreover GI microbiota perform many important functions like protection, immune development and metabolism, which together have an enormous effect on host nutrition and health condition [104-106]. Previous studies suggest that human and bovine milk proteins prevent the adhesion and colonisation of pathogenic bacteria in the GI tract [107-109] and promote the growth of beneficial bacteria [110]. As knowing that GI microbiota have several physiological functions in the human health condition, it can be influenced by Lacprodan® PL-20 milk protein supplementation. Therefore, it will be valuable to study the GI microbiota at different time points across the clinical trial to identify the effect of Lacprodan® PL-20 on indigenes microbial community.

Faecal samples will be collected for the GI microbiota analysis at baseline, 90 days and 180 days to explore the possible effect of Lacprodan® PL-20 on the microbial composition. The microbiota analysis will be carried out by utilising deep next-generation shotgun sequencing [111] of DNA extracted from collected faecal samples. This analysis will provide insight into GI microbiota of the ageing population and also functional characterisation will provide understanding of the potential mechanism by which Lacprodan® PL-20 may influence age-related cognitive decline (ARCD).

#### Biochemical assessment

Haematological testing will be conducted at baseline, 90 days and 180 days in order to further investigate possible mechanisms by which Lacprodan® PL-20 may influence cognitive decline. These measures have been chosen on the basis of current aetiological understanding of brain ageing as well as proposed *in vivo* actions of Lacprodan® PL-20 constituents.

Previous research has demonstrated that administration of PC, a major phospholipid component of Lacprodan® PL-20, can increase the plasma choline as well as brain acetylcholine (Ach) supply [112,113]. Further, elevated levels of the neurotoxic substance HCy have been found to be a risk factor for cognitive decline [48,114-116]. Improved HCy levels have been found to result from increased intake of PC and choline [52,53]. Vitamin B12, which is present in high quantities in dairy products [117], has also been found to be effective in reducing HCy in elderly populations [118]. For these reasons plasma choline as well as B Vitamins and HCy levels will be monitored throughout the study.

Other major contributors to brain ageing are oxidative stress [119,120] and inflammation [121]. The phospholipids PC and PS have both been found to display anti-inflammatory and antioxidant properties, inhibiting microglial activation as well as superoxide and nitric oxide production [122]. Endogenous antioxidant glutathione (GSH) is the most abundant antioxidant in human cells, which plays a central role in defence from oxidative stress [123]. Under normal physiological conditions the ratio of reduced GSH to oxidized glutathione (glutathione disulphide, GSSG) is as high as 100:1. However, in cases of increased oxidative stress the ratio changes due to increased levels of GSSG or decreased levels of reduced GSH. For this reason peripheral blood levels of GSH as well as the ratio of GSH/GSSG in the blood are good measures of oxidative stress, and have been found to be altered in patients with mild cognitive impairment and AD [124]. Another widely-used biomarker of oxidative stress is F2-isoprostane, which is an excellent *in vivo* measure of lipid peroxidation [125]. Peripheral blood plasma levels of F2 isoprostane have been found to be significantly elevated in mild cognitive impairment [126]. A previous study from our laboratory in elderly participants found plasma F2 isoprostane levels to significantly decline following a 3-month intervention with the antioxidant Pycnogenol [127]. In addition to these measures of oxidative stress, serum measures of inflammation will be provided using the following inflammatory biomarkers: TNF-α, IL-1β, IL-6 and C-reactive protein (CRP). Peripheral levels of these inflammatory biomarkers have previously been found to be elevated in cases of mild cognitive impairment and AD in comparison to healthy age-matched controls [128,129].

